## Abstract

**Background:**

The WHO recognises pesticide poisoning to be the single most important means of suicide globally. Pesticide self-poisoning is a major public health and clinical problem in rural Asia, where it has led to case fatality ratios 20-30 times higher than self-poisoning in the developed world. One approach to reducing access to pesticides is for households to store pesticides in lockable "safe-storage" containers. However, before this approach can be promoted, evidence is required on its effectiveness and safety.

**Methods/Design:**

A community-based cluster randomised controlled trial has been set up in 44,000 households in the North Central Province, Sri Lanka. A census is being performed, collecting baseline demographic data, socio-economic status, pesticide usage, self-harm and alcohol. Participating villages are then randomised and eligible households in the intervention arm given a lockable safe storage container for agrochemicals.

The primary outcome will be incidence of pesticide self-poisoning over three years amongst individuals aged 14 years and over. 217,944 person years of follow-up are required in each arm to detect a 33% reduction in pesticide self-poisoning with 80% power at the 5% significance level. Secondary outcomes will include the incidence of all pesticide poisoning and total self-harm.

**Discussion:**

This paper describes a large effectiveness study of a community intervention to reduce the burden of intentional poisoning in rural Sri Lanka. The study builds on a strong partnership between provincial health services, local and international researchers, and local communities. We discuss issues in relation to randomisation and contamination, engaging control villages, the intervention, and strategies to improve adherence.

**Trial Registritation:**

The trial is registered on ClinicalTrials.gov ref: NCT1146496 (http://clinicaltrialsfeeds.org/clinical-trials/show/NCT01146496).

## Background

Pesticide poisoning is a major public health in rural Asia [1] and a significant burden on health services [2]. In a recent systematic review the global estimate of deaths due to pesticide self-poisoning was between 250-370,000 each year [3]. The WHO recognises pesticide poisoning to be the single most important global means of suicide and has established an initiative aiming to reduce the number of deaths [4]. Several approaches have been proposed to reduce mortality from pesticide self-poisoning [5-7].

Restricting easy access to pesticides in rural households to prevent their use in impulsive self-harm has become a popular recommendation [8-13]. There is convincing evidence that restricting access to commonly used, highly lethal methods of suicide not only reduces method-specific suicide rates, but can also significantly reduce overall rates [8,13-15]. Some of the factors that have been highlighted as determining the impact of modifying access to means include the popularity of the method, the danger associated with the method, levels of impulsivity, the risk of method substitution, and the ease with which it can be implemented [15].

Pesticide self-poisoning is prevalent in Sri Lanka; it is the most common method of suicide [16], is highly lethal [17], and is associated with impulsivity [5,18,19]. One possible consequence of restricting access to pesticides is the substitution of means of self-harm. This might offset the beneficial impact of means restriction if the newly adopted method is more accessible and of higher lethality. However, such effects have not previously been seen in Sri Lanka: the fall in deaths from pesticide self-poisoning seen since 1995 has not been associated with large increases in other methods of suicide [16].

The pesticide industry has long argued for secure storage and the use of locked boxes to prevent pesticide poisoning, and has started projects testing and scaling up the use of safe storage boxes [20]. It has supported a number of meetings on this option in Singapore, Durban, and Geneva [21,22].

There have been several small scale pilot projects with high levels of community acceptability (Table 1) [23-25]. Whilst this approach appears to make good sense, the provision of containers may actually increase the storage of pesticides in or close to the household rather than at a distance in the field thereby increasing the risk of pesticide ingestion at times of stress. Pilot studies in Sri Lanka showed that this indeed happened, with household storage of pesticides (whether locked or unlocked) increased from 0% to between 75-98% over the first few months after provision of the boxes (Figure 1).

**Table 1 T1:** SACTRC and Oxford Centre for Suicide Research (OSCR) safe storage pilot studies in Sri Lanka

Study	Start	Containers	Households*	Follow-up
A. SACTRC [23]	May 2005	• Wood in-house container • Metal in-house container	116 56	24 months
				
B. OCSR [24]	March 2006	• Metal in-house container	362	18 months
				
C. SACTRC [25]	May 2006	• Wood in-house container • Concrete in-field container	53 103	7 months
				

*Households that received particular containers and were using pesticides at 7 months

**Figure 1 F1:**
[figure not shown]
**Household storage of pesticides in pilot studies in Sri Lanka**. **Left - **% of households storing pesticides safely in or around their house in the five studies. **Right - **Comparison of the % of households in Study A storing pesticides in their household (top line) and the % storing pesticides safely locked up (bottom line) after provision of a safe storage container. The hatched area represents households storing unlocked pesticides. ***Note***, there was no change in the number of households that stored pesticides in the house without locking them away. Instead, the intervention markedly increased the absolute number of households storing pesticides in the house, potentially increasing the risk of poisoning if the compliance with locking them away fell away over time.

Although in one of the studies 82% of containers were locked securely at 7 months, by 24 months this had dropped to 55% [23].In addition, the use of the lock may decline over time and households may find it difficult to keep the key hidden from younger household members. Two further studies showed similar patterns in the drop- off in compliance after 12 months [24,25]. So, before this approach is implemented more widely a large scale community trial is required to determine its effectiveness and safety [26].

## Methods/Design

### Study hypothesis

The main study hypothesis is that the introduction of safe storage boxes to households who use or store pesticides will reduce the incidence of pesticide self-poisoning.

### Design

This is a community-based; cluster randomised controlled trial (RCT) of safe storage containers.

### Setting

We have set up the community-based cluster randomised control trial in the Anuradhapura district of Sri Lanka's North Central Province (population: 1,104,664: Census 2001). We plan to recruit approximately 162 villages primarily from the Mahaweli H region, including the divisional secretariats of Thambuthegama, Talawa, Galnewa, Rajanganaya and Nochchiyagama, (total population about 200,000) in the South East area of the district (Figure 2). The trial started recruiting households on 31 December 2010.

**Figure 2 F2:**
[figure not shown]
**Distribution of study areas and hospitals in the Anuradhapura District of Sri Lanka**. Five study areas divisional secretariats (Thambuthegama, Talawa, Galnewa, Rajanganaya and Nochchiyagama) and additional neighbouring division of Ipalogama where additional households may be recruited. The map also shows the fifteen peripheral hospitals (Rural, District, Primary and Base hospitals) within, or neighbouring, the study area that are used to identify cases of poisoning and self-harm.

This irrigated rural region uses large amounts of pesticides, has high rates of self-poisoning [1,17,18] and was the location of earlier pilot safe storage trials [23-25]. The villages recruited to the pilot studies will be excluded from the current trial.

### Inclusion and exclusion criteria

All villages within the five Divisional Secretariats will be eligible for study entry except those recruited to our previous pilot studies. If necessary, additional households will be recruited from Ipalogama, a neighbouring divisional secretariat, to ensure an adequate number of households are enrolled. Those households in the intervention arm where farm workers are resident and where pesticide use or storage is reported will be eligible for a lockable safe storage box. Households where there is no adult available to provide consent will be excluded.

### Recruitment and baseline survey

An estimated one hundred and sixty-two villages are being recruited from five divisions of Anuradhapura district. The recruitment of villages is being undertaken in a rolling programme across the study area and the five Divisional Secretariats' will be divided roughly in half, creating 10 bands. All households will be approached and given a brief introduction and the householders' invited to verbally consent to participation.

A census is being performed, collecting baseline demographic (name and age/date of birth of all adults and children), socio-economic status, pesticide usage, previous self-reported self-harm and alcohol use data from each participating household. The questionnaire was tested in surrounding villages to ensure the questions were easily understood and the responses captured the relevant options in the local context. The data is being collected using a Juno Trimble survey device (http://www.trimble.com/junosb.shtml), allowing on-going quality assurance, monitoring of survey coverage, and recording of GPS coordinates for later mapping using a geographical information system. If a household refuses to participate only their location is recorded to ensure they are excluded from further follow up.

By collecting baseline survey data into a handheld recorder, transcribing errors are avoided by then downloading data directly into the main study database. In order to assess the accuracy of the data obtained, key data items (age and sex of each household member, quality of housing, and ownership of vehicles.) are validated by data collection managers revisiting a randomly selected (2%) sample of households in each village. The questionnaire is administered in Sinhala by a team of data collectors (high school graduates) recruited from the surrounding areas and trained in field research techniques and use of the questionnaire. Supervisors are present in the field to address any issues when administering the questionnaire or other issues arising from the fieldwork. Subsequent retraining is undertaken on a monthly basis to ensure compliance with the study protocol. Data is managed independently of the field team in Colombo and will be checked using a number of queries in Microsoft Access to improve accuracy.

### Randomisation

In this cluster randomised trial, villages (or groups of adjoining villages where boundaries are blurred; see Discussion) are the randomisation unit and are allocated to either the intervention or comparison group. Large imbalances between study arms in the number of allocated villages, the number of villagers in households eligible for a box, and the previous history of pesticide self-harm in the village, are avoided by the method of minimisation. Prior to allocation the village is added to each arm in turn and the differences on the three minimisation variables calculated. The odds of randomly allocating that village to one arm rather than the other is then modified to give an improved chance of the allocation, which achieves better balance between the two arms.

Steps have been taken to avoid selection bias during random allocation: (i) Villages are only randomised once household demographic data has been collected from all villages in the study administrative band; after this has been done villages cannot be withdrawn from or added to the study; (ii) The UK-based study statistician, who does not come into contact with study villages or data collectors, uploads data on the minimisation variables to an automated computer randomisation programme. Hence allocation concealment is ensured, it neither being possible to predict allocations, nor to withdraw or recruit villages or households once the allocation is known.

### Trial intervention

Following several pilot studies [23-25] of the acceptability and use of safe storage devices, we developed and field tested a storage container made from UV-resistant plastic that can be placed outside the house (in the home garden or field) and partially buried underground. Lock damage and corrosion were identified as a problem in the pilot studies. We have therefore designed the container to have two lids: an inner lid that can be locked and an outer black lid to protect the lock against weather or soil damage (Figure 3).

**Figure 3 F3:**
[figure not shown]
**Safe storage device for agrochemicals in Sri Lanka**. The UV-resistant plastic pesticide storage container to be used in this study. A) Device before installation: the metal bar at the base secures the device from theft. B) Device buried with two lids to protect the padlock from weather damage. C) Device can store several large and small bottles of pesticides. *Copyright [name]*.

Following randomisation the GN official (lowest level of civil administration) in the villages in the intervention arm is informed and arrangements made for distribution of the devices to eligible households. A small demonstration is given and a range of materials are utilised to ensure the box is installed and used correctly. Efforts are made to ensure that the boxes are installed in field, compound or house and members of the distribution team follow up in the village to ensure all eligible people receive a box. Where the distribution team is uncertain about the eligibility of households they are required to bury the device to reduce the likelihood of contamination. Further promotion after distribution is limited to six monthly activities of limited scale in the villages.

As an evaluation of intervention adherence, a small sub-study in approximately five villages will be undertaken to examine the use of the safe storage device. Household opinions on the usefulness of the devices will be elicited through a survey and focus groups. In addition, the demographic survey will be repeated in each village at the end of the study to better estimate person years of follow-up and to observe whether the containers are still being used.

### Outcomes

Our primary and secondary outcome measures are objective. The primary outcome is the incidence of pesticide self-poisoning, both fatal and non-fatal, amongst villagers aged 14 years or older, over the three-year study period. Secondary outcomes will include the incidence of: pesticide poisoning in general (deliberate and accidental, all ages), self-harm (all methods, both fatal and non-fatal), self-poisoning (all substances) and pesticide poisoning in children (younger than 14 years).

Data on cases of fatal and non-fatal pesticide self-poisoning, accidental poisoning and self-harm will be prospectively collected from several sources:

• *Hospitals: *Patients admitted to hospital will be identified routinely at Anuradhapura Teaching Hospital (where SACTRC have an ongoing cohort study). Clinical research assistants have been employed to attend daily ward rounds in the four medical wards and weekly checks of admission books in Surgical, Pediatric, Intensive Care wards and the Morgue at Anuradhapura Teaching Hospital; they will be unaware of the village allocation. All rural peripheral hospitals in the district have been visited at least every month by researchers in a previous project (trial registration number ISRCTN73983810) to identify poisoning admissions; this will be continued in 13 hospitals in our study area. Field research officers will visit every peripheral hospital in the study area and neighboring hospitals to identify cases through checks of the admission and transfer books and discussion with relevant staff.

• *Community: *We will visit a sample of villages (10%) at least every two months to interview local key informants including the GN official, public health midwife and local health committee members (Suwasahana). These local committees will assist in linking cases to their households. If this approach improves the linking of cases to their households, we will seek to work with further community health committees during follow-up.

• *Coroners: *Deaths that occur before hospital presentation will be identified through review of the district coroners' and magistrates' records, as has been documented in another study [27].

Community-based studies in Sri Lanka indicate that practically all patients with poisoning are taken to hospital ([name], unpublished data) and about 80% are transferred to the tertiary hospital [28]. Health care is free and usually available within one hour, and few barriers exist to hospital presentation [29].

The linking of individual cases of self-poisoning and self-harm back to the census data collected from households is complex due to imprecise demographic information. There are complex naming practices, poor recollection of birth dates and no unique identification numbers. Therefore a computer algorithm will match cases to census data using partial names and homophones, approximate ages and partial addresses to generate a list of possible matches that will then be checked manually.

### Pre-specified statistical analysis plan

The primary analysis will follow the intention-to-treat principle, comparing the observed incidence of self-harm using pesticides between individuals in villages allocated to the intervention, and individuals in villages allocated to the control arm. A Poisson regression model will be employed, with the standard errors inflated to accommodate the clustered design. This analysis will be adjusted for minimisation variables used in the random allocation and for seasonal variation in the incidence of pesticide self-poisoning. This same approach will also be used for the secondary outcome measures.

Pre-specified subgroup analyses will investigate whether the effectiveness of the safe storage intervention is modified by the village-level historical rate of self-poisoning (established in the baseline survey) and proportion of households provided with a locked box. We will perform a sensitivity analysis excluding the five intervention villages where sub-studies are undertaken as their participation may increase household compliance with safe storage.

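### Villages are randomised in ten geographic bands at different dates, but the fixed adjustment set leaves out band and calendar period, which gives up some precision without biasing the comparison

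*Protocol article*

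**What the plan says.** Under Recruitment and baseline survey, the protocol article describes entry as a "rolling programme across the study area and the five Divisional Secretariats' will be divided roughly in half, creating 10 bands". Under Randomisation it adds: "Villages are only randomised once household demographic data has been collected from all villages in the study administrative band". Band therefore marks where a village lies, roughly when it enters, and the stage at which it is allocated.

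The same section names three minimisation variables. The first two are in the phrase "Large imbalances between study arms in the number of allocated villages, the number of villagers in households eligible for a box", and the third is "the previous history of pesticide self-harm in the village, are avoided by the method of minimisation". Band, division and date are not among them.

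The section headed Pre-specified statistical analysis plan fixes the covariates of the primary model: "This analysis will be adjusted for minimisation variables used in the random allocation and for seasonal variation in the incidence of pesticide self-poisoning". Standard errors are inflated for clustering, and the secondary outcomes use the same approach. Neither band nor calendar period is listed.

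**The concern.** The plan adjusts for variables that shaped the allocation, which is sound practice. Band also shaped it, because allocation proceeds one band at a time, yet it is left out.

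Season does not fill the gap. It describes a pattern that recurs within each year, and over about three years every village passes through much the same seasons. A seasonal term therefore removes little variation between villages, and it cannot represent differences between areas or a change from one year to the next. Area could matter both for the true rate and for case finding, since the Outcomes section relies partly on peripheral hospitals.

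What is at stake is precision. Where arms are balanced within bands, leaving band out keeps area variation that both arms share in the standard error, so the reported interval is wider than the design warrants. Where a band happens to be uneven, a little area or calendar difference enters the contrast by chance.

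**Working it through.** **1. The plan's own figures (Sample size section).** Inputs are 175 and 117 per 100,000 per year, 80% power, 5% two-sided, design effect 1.75, 20% of the intervention arm not using a container, and 5% of the control arm using one. The method is the two-proportion formula with pooled variance and no continuity correction, treating person-years as units.

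- Unclustered: 0.00175 against 0.67 × 0.00175 gives 68,678 (stated 68,676). The rounded 0.00117 gives 68,029, within 1%.
- Clustered: 68,676 × 1.75 = 120,183, as stated.
- Diluted rates: control 0.95 × 0.00175 + 0.05 × 0.00117 = 0.001721; intervention 0.80 × 0.00117 + 0.20 × 0.00175 = 0.001286. These need 124,539 person-years, and 124,539 × 1.75 = 217,943 (stated 217,944).
- Power at 217,944 per arm is 80.0% with design effect 1.75, and 82.5% with the estimated 1.64.

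The sample size stands.

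**2. What band could recover.** Write the design effect as 1 + 0.75, where 0.75 is the between-village part. Let f be the share of that part lying between bands. The document does not give f, so a range is assumed. If the model absorbs it, the new design effect is 1 + 0.75 × (1 − f), and the log-scale interval width is multiplied by √(new design effect / 1.75).

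| Assumed f | Design effect | Interval narrower by | Power |
|---|---|---|---|
| 0 | 1.75 | 0% | 80.0% |
| 10% | 1.675 | 2.2% | 81.7% |
| 20% | 1.60 | 4.4% | 83.4% |
| 30% | 1.525 | 6.6% | 85.1% |
| 50% | 1.375 | 11.4% | 88.5% |

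At the planned diluted rate ratio, 0.001286 / 0.001721 = 0.75, the 95% interval is 0.609 to 0.917 with design effect 1.75, 0.612 to 0.913 with 1.675, and 0.623 to 0.896 with 1.375.

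**3. Why these are upper limits.** Village self-harm history is already in the model. Suppose, for illustration, that it removes half of the between-village part, leaving a design effect of 1.375. If 25% of the remainder lies between bands, the new value is 1 + 0.375 × 0.75 = 1.281, and √(1.281 / 1.375) = 0.965, a gain of 3.5%. Without that credit, the same 25% gives 1.5625 and √(1.5625 / 1.75) = 0.945, a gain of 5.5%. Starting from 1.64 instead of 1.75, the 10% to 50% range gives about 2% to 10%.

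**4. Balance within bands.** A biased coin acting on the running village count alone was simulated for 162 villages in ten bands of 16 or 17. The mean absolute within-band difference was 3.2 villages under simple randomisation, 1.6 with coin probability 0.7 and 1.0 with 0.8. The protocol does not state its coin probability, and two other variables also drive allocation, so the true figure probably lies between these values.

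**5. Can the model carry the parameters?** Expected events are 217,944 × 0.001721 ≈ 375 and 217,944 × 0.001286 ≈ 280, about 655 in all or 65 per band. Nine band parameters are easily supported for the primary outcome.

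**The case against.** The strongest reply is that nothing here is invalid. Standard errors allow for clustering, the sample size pays for variation between villages, and any chance imbalance in band is sampling error that the interval already covers. Self-harm history is a baseline version of the primary outcome and should take up part of any stable area difference. Outcome history plus season is a defensible covariate set, and the gain from band rests on a variance share that appears nowhere in the document and could be zero. All of this stands. It limits the point to precision and makes the figures upper limits.

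A reader might go further and infer that the arms are unbalanced by area or that a time trend confounds the comparison. The document does not support that. Allocating one band at a time, with minimisation on village count, gives both arms much the same places and roughly the same start times. The trend in the Background, "the fall in deaths from pesticide self-poisoning seen since 1995", concerns deaths, whereas the primary outcome counts fatal and non-fatal episodes. No incidence trend is given, and for the stagger the article gives only the date recruitment began. Calendar effects are plausible but unquantified.

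Two remedies that might seem to follow do not. Altering the minimisation once recruitment is under way would change the allocation method for balance that the running village count largely supplies. Forcing ten band effects on every secondary outcome could fail where events are few, as may happen with poisoning in children under 14, for which no rate is given.

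It could also be said that an article leaves such detail to a fuller plan. Here, however, the article states the covariate set itself, so the choice is open to comment.

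**Conclusion.** The point holds as a modest loss of precision. Band and calendar period are in neither the minimisation list nor the stated adjustment set, although band governs how and when villages are allocated. Under an assumed between-band share of 10% to 50%, including band narrows the log-scale interval by at most about 2% to 11%, and by less if self-harm history already explains area differences. At a share of zero, there is no gain and almost no cost. No systematic bias, invalid interval or shortfall in power is shown. This is an inexpensive improvement to the analysis, not an error that threatens the trial's conclusion.

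**What to change.** In the Pre-specified statistical analysis plan section, add administrative band as a covariate in the primary Poisson model and calendar period beside season. Do the same for secondary outcomes where event counts allow. For sparse outcomes, such as poisoning in children under 14, use division or a random band effect. State this before outcome data are examined by arm.

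Band and dates should already be on record, because allocation depends on them. The cost is a sentence or two in the plan, about nine parameters for band, and a few more for calendar period. The minimisation algorithm and the sample size stay as they are.

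### The primary model takes its covariates from the minimisation list, which includes an arm total that no village has and a head-count that suits a rate poorly; naming the terms would gain a little precision

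*Protocol article*

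**What the plan says.** All references are to the protocol article. Under 'Pre-specified statistical analysis plan' the primary model is described as follows: "A Poisson regression model will be employed, with the standard errors inflated to accommodate the clustered design". On covariates, the same paragraph states: "This analysis will be adjusted for minimisation variables used in the random allocation and for seasonal variation".

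The section does not list the minimisation variables. They stand under 'Randomisation', as three quantities on which imbalance is to be limited. One is the running total of villages already assigned to each arm. Another is a head-count, given as "the number of villagers in households eligible for a box". The last is a record of past events, given as "the previous history of pesticide self-harm in the village".

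Under 'Recruitment and baseline survey' the census records the age of household members and also "socio-economic status, pesticide usage, previous self-reported self-harm and alcohol use data from each participating household". The validation step in that section shows that sex is recorded too. 'Randomisation' states that villages are allocated only after household demographic data are in for the whole administrative band, so these are pre-randomisation values. Apart from self-harm history and the eligible head-count, none of them is named in the primary model.

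**The concern.** The primary outcome is an incidence, so each covariate should describe something that varies between villages and bears on a rate per person-year. Taking the minimisation list over unchanged does this only in part.

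- **Number of allocated villages.** This describes an arm at a moment in the allocation sequence. A single village has no value for it, so that part of the sentence cannot be carried out.
- **Villagers in box-eligible households.** A head-count is sensible for balancing arm sizes. In a rate model it largely measures how big the village is. The share of residents living in pesticide-using households, which could plausibly drive the rate, is not a term.
- **History of pesticide self-harm.** This is a true village attribute and a baseline version of the outcome. 'Randomisation' does not say whether it is a count or a rate; a count would again mix risk with village size.

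What is at stake is precision. The standard errors are inflated for clustering, so any between-village variation that baseline terms could have explained stays in the primary interval. With a log link, adding baseline covariates does not change the rate ratio being estimated, so the gain would not alter the question.

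**Working it through.** **1. Reproduce the planned size ('Sample size').** Inputs: 175 v 117 per 100,000 per year, 80% power, 5% two-sided, design effect 1.75, 20% non-use in the intervention arm, 5% contamination in the control arm.

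- Unclustered, taking a 33% reduction as 175 × 0.67: 68,678 person-years per arm (stated 68,676). 68,676 × 1.75 = 120,183, as stated.
- Diluted rates, with RR = 117/175: control 175 × (0.95 + 0.05 RR) = 172.1; intervention 175 × (0.20 + 0.80 RR) = 128.6. The pooled two-proportion formula gives 124,539; × 1.75 = 217,943 (stated 217,944).

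The figure reproduces with the full design effect of 1.75 and no allowance for covariates.

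**2. How much of the variance lies between villages.** 0.75/1.75 = 43% before any adjustment. Expected events are 217,944 × 172.1/100,000 ≈ 375 and 217,944 × 128.6/100,000 ≈ 280. Then SE(log RR) = √[DE × (1/375 + 1/280)]. At DE = 1.75 this is 0.104, with power 79.7% on the log scale (80.0% by the plan's formula).

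**3. Credit the history term first, since it is already planned.** *Assumption:* history is captured like the outcome over 1 to 3 years and village rates are stable. At 175 per 100,000 a village has 217,944/81 × 0.00175 = 4.71 events in three years, or 1.57 a year. The between-village CV² is 0.75/4.71 = 0.159. The share explained is CV² × events / (1 + CV² × events):

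- one year: 0.25/1.25 = 20%, DE = 1 + 0.75 × 0.80 = 1.60, power 83%;
- three years: 0.75/1.75 = 43%, DE = 1 + 0.75 × 0.57 = 1.43, power 87%.

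The history is self-reported, so the true share may be lower.

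**4. What the head-count misses.** If village size and eligible proportion vary independently, the squared correlation (log scale) of the count with the proportion is about CVp²/(CVp² + CVN²). *Assumptions:* mean proportion 0.8, village SD 0.10 to 0.20 (CVp 0.125 to 0.25), village-size CV 0.3 to 0.7. The range runs from 0.0156/(0.0156 + 0.49) = 3% to 0.0625/(0.0625 + 0.09) = 41%.

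**5. What the eligible proportion could add.** If eligible residents have R times the risk, the CV of the village rate due to the proportion is (R − 1) × SD / [1 + (R − 1) × 0.8].

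- R = 2, SD 0.10: 0.1/1.8 = 0.056; squared, 0.0031; 0.0031/0.159 ≈ 2%.
- R = 4, SD 0.20: 0.6/3.4 = 0.176; squared, 0.0311; 0.0311/0.159 ≈ 20%.

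Apply these shares to what remains after history, with new DE = 1 + (DE − 1)(1 − f) and narrowing = 1 − √(new DE/DE):

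| Extra share f | From DE 1.60 | From DE 1.43 |
|---|---|---|
| 2% | 1.588, 0.4% narrower | 1.421, 0.3% narrower |
| 20% | 1.48, 3.8% narrower, power +2.8 points | 1.344, 3.0% narrower, power +1.9 points |
| 30% (all added terms) | 1.42, 5.8% narrower, power +4.1 points | 1.301, 4.6% narrower, power +2.9 points |

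A simulation with history already in the model, and R of 2 to 4 with SD 0.10 to 0.20, gave a standard error about 0% to 4% lower from rate-form history plus the eligible proportion. This agrees with the first two rows.

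**The case against.** The strongest reply is that nothing here is invalid. Adjusting for the allocation factors and season matches analysis to design, and wanting further prognostic terms is a choice between sound analyses. The exact form of a covariate is often left to a full analysis plan, which is not shown here. The village count would in practice simply not be entered, with no effect on the interval. The subgroup paragraph already speaks of a village-level historical rate and of the proportion of households given a box, so the authors had both forms in mind.

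Most of this stands, and it limits the point to efficiency. It does not remove it. The article itself fixes the covariate set, under a heading that calls it pre-specified, by pointing to a list with an unusable item. The rate and the proportion appear only as effect modifiers in subgroup analyses.

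A reader might infer three stronger things:

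- **That the trial is underpowered.** It is not on this account: the 80% was computed at a design effect of 1.75, set above the estimate of at least 1.64, with no covariate credit.
- **That the estimate is biased.** Nothing in the documents supports this; allocation is random and the effect estimated is the same with or without the extra terms.
- **That better covariates would lift power from 80% to about 85%.** That takes a 30% explained share from a design effect of 1.75 (1 + 0.75 × 0.70 = 1.525), as if the history term were absent.

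Nor do the documents show that age, sex or eligibility predict differences between village rates.

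**Conclusion.** The point holds as a modest forgone gain in precision and a sentence that cannot be carried out in full. One minimisation variable is an arm total. Another is a head-count that largely tracks village size. The most useful predictor, self-harm history, is already in the model and should be credited.

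The gain is roughly 0% to 4% in interval width, or about 0 to 3 power points, for the eligible proportion and rate-form history. It reaches about 6% if all added covariates explain 30% of the remaining between-village variance. These figures rest on assumed values for the share explained by history, the risk ratio of eligible residents, the mean and spread of the eligible proportion, and the spread of village sizes. The documents give none of these.

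**What to change.** In 'Pre-specified statistical analysis plan', replace the reference to the minimisation variables with named terms, and keep season:

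- drop the number of allocated villages as a covariate;
- enter village history of pesticide self-harm as a rate per resident;
- add the baseline proportion of residents aged 14 or over living in box-eligible households, alongside the minimised head-count;
- add age group and sex from the census.

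Keep the model with only the usable minimisation variables (eligible head-count and history, with season) as a sensitivity analysis.

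The cost is wording, and it should be settled before outcome data are seen by arm. The data are already collected before randomisation, though person-years must be split by age group and sex. The statistical price is a few extra parameters against about 162 clusters.
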